## Introduction

Emergency abdominal surgery is associated with increased rates of early and late postoperative complications, particularly the development of postoperative abdominal wall hernias [1]. This study protocol outlines the rationale and design of the PROPHECY trial, which will investigate this issue prospectively. Midline incisional hernias are among the most common complications after laparotomy and are associated with reduced quality of life, chronic pain, and need for complex reoperations [2, 3]. Despite a large number of analyzes on ways to reduce the incidence of this complication, it is still an important surgical problem [2]. Studies encompassing both elective and emergency procedures report postoperative hernia rates ranging from 2% to 40% [4]. This variation may be attributable to the often asymptomatic nature of certain hernias. An example are port-site hernias although generally perceived as rare, may occur more frequently than previously recognised, especially at umbilical sites [5]. Another significant surgical problem is parastomal hernias, occurring in up to 50% of patients with stomas [6]. The variability in reported incidence is also influenced by the method and duration of follow-up. True incidence rates are likely underreported, particularly in emergency surgery patients, where postoperative follow-up is frequently inconsistent or lacking.

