### Study Endpoints

#### Primary Endpoints

• Incidence of incisional hernia at the surgical site
• Incidence of port-site hernia following laparoscopy
• Incidence of parastomal hernia following stoma formation

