### Sample Size Justification

To estimate a 5% precision for postoperative hernia incidence with 95% CI, a minimum of 255 cases is required. For port-site hernias, at least 188 patients are required; for parastomal hernias, 349. For secondary outcomes, the required sample sizes are 255 for SSI and 93 for burst abdomen. Sample size considerations are summarised in Table 1. To detect a moderate effect size (Cohen’s d = 0.3) with 80% power at α = 0.05, the required sample size is.
• Chi-squared test (1 df): 88 patients
• Chi-squared test (5 df): 143 patients
• Student’s t-test: 102 patients

**TABLE 1 T1:** Sample size rationale.

Endpoint	Sample size	Notes
Incisional Hernia	255	To estimate with 5% precision, 95% CI
Port-site Hernia	188	To estimate with 5% precision, 95% CI
Parastomal Hernia	349	To estimate with 5% precision, 95% CI
Surgical Site Infection (SSI)	255	To detect moderate effect size, 80% power
Burst Abdomen	93	To detect moderate effect size, 80% power

The total planned cohort will consist of 500 patients, which ensures sufficient power to assess primary and secondary outcomes while allowing for exploratory and subgroup analyses, including risk factors associated with specific surgical techniques or patient characteristics. This sample size also accommodates a potential dropout rate of up to 10% and supports the development of multivariate models with adequate statistical reliability.

To ensure feasibility across all participating centres, over-recruitment will be limited to a maximum of 50% above the calculated minimum sample size required for primary endpoints.

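### The claim that 500 patients suffice for all primary outcomes is unsupported for parastomal hernia: the 349 required must be stoma patients, about 70% of the cohort, and nothing in the design provides for that share

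*Protocol article*

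**What the plan says.** All on this point stands in the protocol article.

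- **Primary Endpoints** lists three incidences. Two name their own population at risk: "Incidence of port-site hernia following laparoscopy" and "Incidence of parastomal hernia following stoma formation". The third is incisional hernia at the surgical site.
- **Sample Size Justification** sets the target: "To estimate a 5% precision for postoperative hernia incidence with 95% CI, a minimum of 255 cases is required". It continues: "For port-site hernias, at least 188 patients are required; for parastomal hernias, 349". Table 1 repeats 255, 188 and 349 for the three hernia types, each with the note on 5% precision and a 95% CI.
- The same section concludes: "The total planned cohort will consist of 500 patients, which ensures sufficient power to assess primary and secondary outcomes". It adds that this size also absorbs up to 10% dropout and leaves room for subgroup analyses.
- On the upper limit it says that "over-recruitment will be limited to a maximum of 50% above the calculated minimum sample size required for primary endpoints".
- **Inclusion Criteria** admit acute appendicitis, acute cholecystitis, incarcerated hernia, gastrointestinal perforation and bowel obstruction. No stoma criterion, quota, stratum or expected stoma share appears anywhere.

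**The concern.** The section sets 500 against each endpoint's required number as if every enrolled patient counted for every endpoint. For parastomal hernia that is not so. A patient without a stoma cannot develop one and adds nothing to the precision of the estimate. The number to compare with 349 is the number of stoma patients among the 500, and the article neither states nor controls it.

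At stake is one of three primary endpoints. If stoma patients are a minority of the cohort, its incidence will be reported with an interval wider than the one the study says it was sized for, while the published protocol tells readers that the size was adequate. The analysis stage cannot repair this, because it depends on who is recruited.

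**Working it through.** **Inputs.** Required number for parastomal hernia 349, target 5% precision with a 95% CI, total 500 and dropout up to 10% (all Sample Size Justification). Denominator: patients with a stoma (Primary Endpoints). The assumed incidence behind 349 is not stated. The only parastomal rate given is in the Introduction: "Another significant surgical problem is parastomal hernias, occurring in up to 50% of patients with stomas".

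**Step 1: reproduce the plan's figures.** I read 5% as an absolute half-width d = 0.05, so n = 1.96² p(1−p)/0.05². The incidence p has to be solved from each stated n:

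| Stated n | Implied p | Check |
|---|---|---|
| 255 (incisional) | about 0.21 | p = 0.21 gives 254.9 |
| 188 (port-site) | about 0.143 | p = 0.143 gives 188.3 |
| 349 (parastomal) | about 0.35 | p = 0.35 gives 349.6 |

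So 349 matches the usual formula at an incidence near 35%. That is credible as a rate among stoma patients, given the cited figure of up to 50%. It is not credible as a rate in a cohort that includes appendicitis and cholecystitis. The formula and the endpoint definition point to the same denominator.

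**Step 2: stoma share needed.**

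- No dropout: 349/500 = 69.8%.
- After 10% dropout: 500 × 0.9 = 450, and 349/450 = 77.6%. Equivalently, 349/0.9 = 387.8, so 388 stoma patients enrolled.
- If the cited upper rate of 50% had been used, n = 1.96² × 0.25/0.05² = 384.1, so 385, or 385/500 = 77.0% before dropout.

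As an illustration, if every perforation and obstruction patient had a stoma and nobody else did, those two indications would have to supply about 70% to 78% of the cohort.

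**Step 3: precision at other shares.** The stoma share is not in the documents, so the shares below are assumptions. Half-width = 1.96 √(0.35 × 0.65/n), with n = share × 450 (left unrounded at 5%):

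| Assumed stoma share of 450 | n | 95% half-width (points) |
|---|---|---|
| 5% | 22.5 | ±19.7 |
| 10% | 45 | ±13.9 |
| 20% | 90 | ±9.9 |
| 30% | 135 | ±8.0 |
| 50% | 225 | ±6.2 |
| 77.6% | 349 | ±5.0 |

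**Step 4: total that 349 stoma patients would require, before dropout.** 349/0.10 = 3,490 at a 10% share; 349/0.20 = 1,745 at 20%; 349/0.30, rounded up, = 1,164 at 30%; 349/0.50 = 698 at 50%.

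**The case against.** The best defence is that the stoma share is unknown, so the target is not shown to be out of reach. A cohort in which 70% have a stoma is arithmetically possible, and at a 50% share the shortfall is modest (±6.2 against ±5). The study is also observational, and its Statistical Analysis section already reports proportions with 95% confidence intervals, so the precision actually achieved will be visible.

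The first part stands as a limit on wording: one may not say that 500 cannot deliver the precision, only that it does so at a share of about 70% or more, for which nothing in the plan provides. The second part does not rescue the sentence, because the article asserts adequacy in advance. Nor is this detail left to a fuller document: the required number, the total and the conclusion are all printed, and the conclusion does not follow.

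Four stronger readings are tempting but not supported:

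- **The planned 500 breaks the over-recruitment cap.** It would if the cap were taken from 255 (1.5 × 255 = 382.5) or 188 (1.5 × 188 = 282). The minimum that serves all the primary endpoints is the largest, and 1.5 × 349 = 523.5 is above 500. The wording is ambiguous, not contradictory.
- **The incisional and port-site targets nearly exhaust the evaluable cohort.** The sum 255 + 188 = 443 of 450 matters only if incisional hernia is counted in open cases alone. The endpoint says only that it is at the surgical site, and the 255 is introduced for postoperative hernia in general, so the groups need not be exclusive.
- **The port-site and parastomal targets together exceed the total.** 188 + 349 = 537, but a patient may have both laparoscopy and a stoma. The targets fit if at least 537 − 500 = 37 patients have both (537 − 450 = 87 after dropout).
- **The sentence also fails for the secondary outcomes.** The stated needs for surgical site infection (255) and burst abdomen (93) both lie within 450 evaluable patients, and the denominator problem does not extend to them.

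**Conclusion.** The concern holds for parastomal hernia, in conditional form. The article's statement that 500 patients suffice for the primary outcomes is wrong as written, because meeting its own figure of 349 needs stoma patients to be about 70% of those enrolled, or 78% of those evaluable after 10% dropout, and the design contains nothing that would produce such a share. Across assumed shares of 5% to 50% of 450, the half-width is ±19.7 to ±6.2 points. It is about twice the ±5 target at 20% and nearly four times at 5%.

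The needed shares of 69.8% and 77.6% rest only on the stated 349, 500 and 10% and on the endpoint definition. The half-widths rest further on three assumptions: 5% means an absolute half-width, the incidence is the back-solved 35%, and dropout is the same in stoma patients as in the rest. The finding is about precision; the article's word power is loose for an incidence estimate.

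**What to change.** 1. Restate the Sample Size Justification and Table 1 by at-risk denominator: patients with a surgical incision that counts for incisional hernia, laparoscopic patients, and stoma patients. For each, give the assumed incidence, the expected number after 10% dropout and the 95% half-width that this number yields.
2. For parastomal hernia, state the expected stoma share and report the real expected precision, for example ±13.9 points if 45 stoma patients are evaluable. It can remain a primary endpoint on those terms.
3. Limit the adequacy sentence to the endpoints for which the expected denominator reaches the stated number. It need not be deleted for surgical site infection and burst abdomen.
4. Optionally, give the over-recruitment cap as one explicit total, so that it is clear which minimum it refers to.

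The cost is wording in one section and one table, and a less favourable stated precision for one primary endpoint. No extra patients are needed.

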### Authorship Criteria

Centres enrolling ≥40 patients may nominate two named authors. Centres recruiting 20–39 patients may nominate one named author. Centres enrolling fewer than 20 patients will be included in the collaborative authorship group.

## Discussion

The PROPHECY trial is uniquely positioned to provide high-quality prospective data on the incidence and risk factors for postoperative hernias in emergency abdominal surgery. This area of surgical care remains underrepresented in current literature, where most evidence derives from elective procedures, despite the fact that emergency settings present unique challenges related to patient stability, contamination, and time constraints.

Patient-related risk factors such as obesity, smoking, immunosuppression, and malnutrition are well-established contributors to impaired wound healing and hernia formation [4, 7, 11]. Yet in the emergency setting, prehabilitation and optimisation are rarely feasible. Identifying high-risk patients based on baseline characteristics may enable the development of targeted intra- and postoperative strategies.

The adoption of the “small bites” technique in fascial closure has been shown to reduce the risk of incisional hernia in elective settings [8, 9], yet its effectiveness in the context of emergency procedures remains to be confirmed. In their meta-analysis, Henriksen et al. demonstrated that small bites using slowly absorbable sutures reduced hernia risk significantly compared to larger bites [8]. However, most trials excluded contaminated or emergency cases. The PROPHECY trial will help determine whether these findings translate to emergency settings where tissue handling is often suboptimal.

Port-site hernias, while historically underestimated, may occur in up to 30% of patients after laparoscopic procedures depending on the size and location of trocar incisions [5, 12]. The decision to suture fascial defects greater than 10 mm is based on such data and is now considered best practice [9]. However, data on port-site hernias from emergency laparoscopies remain limited. The PROPHECY trial will provide new insight into this complication in urgent settings.

Parastomal hernias remain another prevalent but under-reported complication. A study by Antoniou et al. found that up to half of patients with permanent stomas develop a hernia at the stoma site [6]. Evidence supports the use of prophylactic mesh in elective stoma formation to reduce this risk [6, 13], but the safety and feasibility of mesh use in emergency stoma creation is still debated due to concerns regarding infection. A meta-analysis by Elzeftawy et al. demonstrated that mesh implantation—particularly in the retromuscular position—significantly reduces the risk of parastomal hernia without increasing the incidence of surgical site infections [13].

One of the most important modifiable factors identified in the literature is surgical site infection (SSI), which significantly increases the risk of incisional hernia development [7, 12]. The use of prophylactic negative pressure wound therapy (NPWT) on closed incisions has shown promise in reducing SSI rates, particularly in high-risk or contaminated fields [14]. Nevertheless, adoption of NPWT in emergency settings remains inconsistent. PROPHECY will capture detailed data on the use of NPWT and its association with hernia and wound-related outcomes.

The inclusion of burst abdomen as a secondary endpoint reflects the growing awareness of this severe complication. Kvist et al. recently reported that burst abdomen following emergency laparotomy occurred in 4.4% of patients and was associated with significantly higher rates of morbidity and mortality [10]. This underlines the importance of optimal fascial closure and early identification of wound dehiscence in this population.

Another area of interest is postoperative care, including the use of abdominal binders and guidance on physical activity resumption. While widely practised, there is limited high-quality evidence supporting their role in preventing hernia formation [2, 9]. PROPHECY will contribute to clarifying the effectiveness of these interventions.

Finally, the multicentre, prospective design and robust sample size calculation of the PROPHECY trial will allow for meaningful subgroup analyses and generalisable conclusions.

By identifying both patient- and procedure-related modifiable risk factors, this study has the potential to inform the creation of specific guidelines for hernia prevention in emergency surgery, where currently none exist.

## Data Availability

The original contributions presented in the study are included in the article/supplementary material, further inquiries can be directed to the corresponding author.
